## 1. Introduction

The life expectancy of individuals with severe mental disorders is estimated to be 20 [1] to 30 [2] years shorter than that of the general population, with evidence suggesting that this disparity has widened in recent decades [3].

Cardiovascular and metabolic diseases are the main causes of death in this population group [4], and having a diagnosis of psychosis is considered a risk factor for the development of these diseases [5]. It is also a risk factor for death from cardiovascular or cerebrovascular events [6].

Metabolic syndrome (MetS), a common cause of cardiovascular and metabolic diseases, develops in one out of every three individuals experiencing psychosis, nearly doubling the odds compared to the general population [7,8]. MetS includes central obesity, increased fasting glucose, dyslipidemia, and hypertension, with insulin resistance playing a central role in various tissues of the body [9,10]. Different definitions have been proposed with similar criteria to diagnose MetS, which involve waist circumference, blood triglyceride levels, HDL cholesterol, fasting glucose, and systolic and diastolic blood pressure biomarkers [11,12,13].

In people who experience psychosis, one of the causes of MetS is the deregulation of glucose metabolism induced by antipsychotic treatment, especially second-generation antipsychotics [14]. In people who have experienced a first psychotic episode, the first year of treatment is crucial for weight gain and the establishment of metabolic alterations [15], with early insulin resistance being a predictor of weight gain and increased waist circumference [16], related to the alteration of hunger regulation [17]. With some exceptions such as Ziprasidone and Lurasidone, all antipsychotics cause significant weight variation, with a greater effect seen in the case of Clozapine and Olanzapine [18].

There is also evidence suggesting that the altered metabolic parameters may not only be due to antipsychotic treatment [19], but also involve other systems beyond the central nervous system in individuals with psychosis [20]. Poor dietary habits [21] or sedentary behavior, closely related to the negative symptoms of psychotic processes such as a lack of motivation or cognitive deterioration, have also been associated with MetS. Additionally, low economic income has been correlated with worse metabolic parameters [22].

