### 2.7. Instruments and Variables

Sociobiographic data will be collected, including sex, age, marital status, living arrangement, educational level, medical diagnosis, time since the beginning of treatment, substance use, antipsychotic type and dose, mood stabilizer use, and whether patients are assisted by a primary caregiver (considered as such if they assist in 4 of the first 6 consultations).

The primary outcome will be weight loss, with a reduction of 5% considered clinically significant [38]. Secondary outcomes will include the establishment or non-establishment of metabolic syndrome according to the International Diabetes Federation (IDF) criteria [12], which consist of abdominal obesity (abdominal circumference ≥ 94 cm in men and ≥80 cm in women) plus two of the following four factors: (i) elevated blood triglycerides (≥150 mg/dL or treatment for it); (ii) decreased HDL-c (<40 mg/dL in men and <50 mg/dL in women); (iii) high blood pressure (systolic blood pressure ≥ 130 mmHg and diastolic blood pressure ≥ 85 mmHg or antihypertensive treatment); and (iv) elevated fasting glucose (≥100 mg/dL or previous diagnosis of type 2 diabetes).

Anthropometric variables (weight, height, BMI, waist circumference) and vital signs (resting blood pressure) will be measured using calibrated equipment provided by the hospital.

Laboratory values (fasting blood glucose, glycosylated hemoglobin, triglycerides, HDL, HDL/LDL ratio, C-reactive protein) will be collected in accordance with hospital policy.

To measure psychopathology, the Positive and Negative Syndrome Scale (PANSS) will be used. This scale consists of 30 items divided into three subscales: positive, negative, and general. The positive subscale measures symptoms such as hallucinations and delusions, the negative subscale measures symptoms such as flat affect and lack of motivation, and the general subscale measures symptoms such as agitation and hostility [37].

Depressive symptoms will be assessed using the Hamilton Depression Rating Scale (HAM-D), which consists of 17 items, with higher scores indicating greater severity of symptoms [39].

The EuroQol-5D (EQ-5D) scale will be used to evaluate a person’s subjective well-being in relation to their health. The scale consists of five dimensions: mobility, self-care, usual activities, pain/discomfort, and anxiety/depression [40].

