### 2.9. Power and Sample Size

We aim to detect a 5% difference in total weight, considering this to be clinically significant [36]. Using a power of 80%, a bilateral alpha of 5%, and assuming a standard deviation of 7.5% in an area where evidence is limited (weight loss in people who have experienced a first psychotic episode). A sample size of 74 participants will be required to detect this difference. Assuming a dropout rate of 20%, we aim to recruit a total of 88 participants, with 44 in each group.

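### The high-blood-pressure factor of metabolic syndrome joins systolic and diastolic elevation with *and*, so as written an untreated participant with only one raised pressure does not meet it

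*Protocol article*

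**What the plan says.** Section 2.7 (Instruments and Variables) of the protocol article names metabolic syndrome status first among the secondary outcomes: "Secondary outcomes will include the establishment or non-establishment of metabolic syndrome". It attributes the rule to a published source, "metabolic syndrome according to the International Diabetes Federation (IDF) criteria [12"], and then writes the rule out with cut-offs. Abdominal obesity is required, "plus two of the following four factors": triglycerides, HDL cholesterol, blood pressure and fasting glucose. The blood-pressure factor reads "systolic blood pressure ≥ 130 mmHg and diastolic blood pressure ≥ 85 mmHg or antihypertensive treatment".

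The only other description of the blood-pressure criterion is in the Introduction, which says that the various definitions involve "systolic and diastolic blood pressure biomarkers". That lists the two measurements and does not say how they combine. Nothing else in the article restates or corrects the rule in Section 2.7.

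**The concern.** The two pressures belong to the same person at the same visit, so the word between them decides who is classified as positive. With *and*, an untreated participant must exceed both thresholds. A reading of 160/80 or 125/95 then fails a factor named high blood pressure.

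The outcome is binary and needs two of four factors, so one factor can decide a participant's status. Metabolic syndrome risk is also part of the main aim at the end of the Introduction. With 88 participants planned, a handful of changed classifications is visible in the result. If the cited definition accepts either pressure, the reported status would not be the outcome that the article names.

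This is not a detail left for a fuller document. The article states the derivation completely, and the issue is what it states.

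**Working it through.** **1. What the text implies, without any assumption.** Let S mean systolic ≥130 mmHg, D mean diastolic ≥85 mmHg and T mean antihypertensive treatment.

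| Participant | S | D | T | As written: (S and D) or T | Either pressure: S or D or T |
|---|---|---|---|---|---|
| 160/80, untreated | yes | no | no | not met | met |
| 125/95, untreated | no | yes | no | not met | met |
| 135/90, untreated | yes | yes | no | met | met |
| any reading, treated | – | – | yes | met | met |

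Everyone who meets the written rule meets the either-pressure rule, so the written rule can never give more cases. The composite differs only for an untreated participant with exactly one raised pressure, abdominal obesity, and exactly one of the other three factors. With none of the other three, neither rule gives metabolic syndrome; with two or more, both do.

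**2. The article's own computed figure.** Section 2.9 gives no figure for metabolic syndrome or blood pressure. Its only calculation concerns weight: "We aim to detect a 5% difference in total weight", "assuming a standard deviation of 7.5"%, 80% power and 5% two-sided alpha. The normal approximation gives n per arm = 2 × (1.960 + 0.842)² × 7.5² / 5² = 35.3, so 36 per arm and 72 in total. The t-test version gives 36.3, so 37 per arm and 74 in total, as stated. None of these inputs involves blood pressure, so the point leaves the sample size alone.

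**3. Illustration of size. All inputs in this step are assumptions.** Pressures are bivariate normal with SDs 13 and 9 mmHg, means from 118/74 to 126/80 and correlation 0.5 to 0.8, and nobody is treated. Abdominal obesity is 50%, triglycerides 30%, HDL 30% and glucose 15%, all independent.

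For the three other factors:
- P(exactly one) = 2 × 0.3 × 0.7 × 0.85 + 0.7 × 0.7 × 0.15 = 0.357 + 0.0735 = 0.4305
- P(two or more) = 1 − 0.7 × 0.7 × 0.85 − 0.4305 = 0.153

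Metabolic syndrome rate = 0.5 × [0.153 + 0.4305 × P(blood-pressure factor)].

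Example at 122/77 with correlation 0.6: P(S) = 0.269, P(D) = 0.187, P(both) = 0.115 and P(either) = 0.342.
- *and*: 0.5 × (0.153 + 0.4305 × 0.115) = 0.101
- *or*: 0.5 × (0.153 + 0.4305 × 0.342) = 0.150
- Difference: 0.5 × 0.4305 × 0.227 × 88 = 4.3 participants

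| Mean, correlation | Factor met, *and* | Factor met, *or* | Syndrome, *and* | Syndrome, *or* | Changed, of 88 | Share of *or* cases |
|---|---|---|---|---|---|---|
| 118/74, 0.8 | 8.2% | 20.7% | 9.4% | 12.1% | 2.4 | 22% |
| 118/74, 0.5 | 5.2% | 23.7% | 8.8% | 12.8% | 3.5 | 31% |
| 122/77, 0.6 | 11.5% | 34.2% | 10.1% | 15.0% | 4.3 | 33% |
| 126/80, 0.8 | 23.5% | 43.4% | 12.7% | 17.0% | 3.8 | 25% |
| 126/80, 0.5 | 18.0% | 48.9% | 11.5% | 18.2% | 5.8 | 37% |

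**4. Sensitivity to prevalence.** The Introduction says that about one in three people with psychosis develops metabolic syndrome, well above the rates in step 3. Assumed rates that come close to this are abdominal obesity 75%, triglycerides 45%, HDL 45%, glucose 20%, and blood-pressure factor 9% (*and*) versus 29% (*or*).
- P(exactly one other) = 2 × 0.45 × 0.55 × 0.8 + 0.55 × 0.55 × 0.2 = 0.4565
- P(two or more others) = 1 − 0.55 × 0.55 × 0.8 − 0.4565 = 0.3015
- *and*: 0.75 × (0.3015 + 0.4565 × 0.09) = 0.257
- *or*: 0.75 × (0.3015 + 0.4565 × 0.29) = 0.325
- Difference: 0.0685 × 88 = 6.0 participants, and 0.0685 / 0.325 = 21% of either-pressure cases

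**The case against.** The same sentence uses *and* loosely to join the waist thresholds for men and for women, which are plainly not required together. The sentence is also governed by the cited definition. The word may therefore be a drafting slip, and whoever derives the outcome may follow the source and accept either pressure. This is possible, but it does not remove the defect. One person cannot be subject to both waist thresholds, so that *and* is harmless, whereas both pressures apply to the same person. If it is a slip, it should be corrected before the outcome is derived.

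A reader might infer more than the article supports, in three ways.

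- That metabolic syndrome *is* under-counted and the rates will not be comparable with other work. This needs a reference rule in which either pressure suffices. The article states none, and the cited definition is not available here.
- That the phrase has a second reading, with systolic elevation always required and treatment replacing only the diastolic criterion. The parallel items argue against it: for triglycerides and glucose, treatment or a prior diagnosis is an alternative to the whole numeric criterion.
- That a fixed share of cases, such as three in ten, is missed. The share moves with the assumed rates. The components are modelled as independent, although the Introduction links them through insulin resistance.

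The limits on consequence also stand. One of four factors in one secondary outcome is affected, and both arms are scored by the same rule, so no bias between arms is shown. Resting blood pressure is measured in any case, so no data are lost.

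**Conclusion.** The point holds as a badly fixed scoring rule. It is certain from the text that an untreated participant with one raised pressure fails the factor as written, and that the rule can only give the same number of metabolic syndrome cases as an either-pressure rule, or fewer. Whether that is an error relative to the cited definition remains open until the source is checked.

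The size cannot be derived from the article. Under the assumptions shown, roughly 2 to 6 of 88 participants would change status. That is about two to three in ten either-pressure cases, with 37% in the most extreme setting tried. The consequence is confined to the secondary metabolic syndrome outcome. The weight outcome and the sample size of 74 evaluable participants do not depend on it.

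**What to change.** Before deriving the outcome, compare the connective in Section 2.7 with the International Diabetes Federation definition that the article says it applies. If that source accepts either pressure, replace *and* with *or*. Whichever rule is confirmed, write it so that only one combination of systolic pressure, diastolic pressure and treatment is possible, for instance as a lettered list, and derive metabolic syndrome status from that rule at every assessment.

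The cost is one phrase in Section 2.7 and one line of derivation code. Table 1 already schedules blood pressure at weeks 1, 24 and 48, so no new measurement is needed, and status already derived can be recomputed from the recorded pressures.

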### 2.8. Statistical Analysis

Categorical variables will be described as frequencies and percentages, while quantitative variables will be described as means and standard deviation (or medians and interquartile ranges where appropriate). Categorical variables will be compared using chi-square analysis or Fisher’s exact test, and quantitative variables will be compared using Student’s *t*-test, ANOVA, or the Mann–Whitney rank-sum test.

To compare changes in outcome variables between groups and over time, a multivariate mixed-effects model with repeated measures (linear or logit, depending on the characteristics of the variable) will be applied. Statistical significance will be assumed if the two-sided *p*-value is <0.05. The main analysis will assess the association between the study group and significant weight loss, defined as losing 5% of the original body weight.

To account for the potential effect of antipsychotics on weight and metabolic parameters, antipsychotics will be categorized as weight-increasing, weight-sparing, or as having non-conclusive effects. Sensitivity analyses will be conducted to examine the effect of each category on the outcomes. Categorization will be based on a review of previous evidence [42]. The use of weight-increasing antipsychotics in combination with weight-sparing antipsychotic use will be coded as weight-increasing antipsychotic use. The cumulative exposure of chlorpromazine-equivalent doses will then be calculated for each antipsychotic category in every patient [43].

Sensitivity analyses will also be conducted for each of the variables included in the previous section.

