### 2.5. Intervention

The study intervention will consist of a series of 8 nursing consultations with a specialized mental health nurse, who is trained in teaching healthy habits to individuals with psychosis and understands the unique factors influencing this group. The nurse will also be skilled in using the therapeutic relationship as a tool for habit modification.

During the first two months, 4 consultations will be held, focusing on educating patients about dietary habits based on the carbohydrate–insulin theory of obesity and physical activity, following a manualized intervention previously designed by a team composed of a mental health nurse, a nutrition and dietetics graduate, and a psychiatrist. This guide has been designed based on the consensus report of the American Diabetes Association for nutrition therapy for diabetes and prediabetes [26], as well as incorporating insights from clinical experience with individuals with a first episode of psychosis. The next two visits will take place 3 and 4 months after the first visit, respectively. Visit 7 will be held after 6 months to evaluate the intervention’s effectiveness, and visit 8 at 12 months. During all visits, weight will be monitored as a reinforcement element.

At the beginning of the study, and at 6 and 12 months from the start of the intervention, a battery of tests will be conducted, including analytical samples, vital signs, anthropometric measurements, and scales to assess psychopathology, quality of life, and level of physical activity.

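### For continuous outcomes, section 2.8 compares changes over time and gives the outcome's own baseline value no stated role; adjusting for it would gain precision at no cost, by an amount that depends on an unstated correlation

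*Protocol article*

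**What the plan says.** Section 2.8 (Statistical Analysis) gives the aim of the longitudinal model as "To compare changes in outcome variables between groups and over time", and says that "a multivariate mixed-effects model with repeated measures (linear or logit, depending on the characteristics of the variable) will be applied". It lists no fixed effects. Baseline is not named as a covariate and not ruled out as one, and nothing is said about whether the arms share a baseline mean. The simpler tests in the same section (t-test, ANOVA, Mann–Whitney) are named without adjustment. Antipsychotic category gets a detailed sensitivity analysis. A closing sentence promises further sensitivity analyses on the variables of the preceding section, without saying how they would enter.

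The primary comparison is binary: "The main analysis will assess the association between the study group and significant weight loss, defined as losing 5% of the original body weight".

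Baseline values will exist. Section 2.5 states: "At the beginning of the study, and at 6 and 12 months from the start of the intervention, a battery of tests will be conducted". The battery covers laboratory tests, vital signs, anthropometry and scales, and Table 1 schedules the same items.

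**The concern.** A mixed model that treats baseline as one more response and lets each arm have its own baseline mean estimates the treatment effect as a difference in changes. It makes no use of the fact that randomisation gives the arms the same expected baseline. A chance difference at baseline then passes into the effect estimate through regression to the mean. Using the baseline value as a covariate, or imposing a common baseline mean, removes that component.

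At stake is the precision of the continuous secondary outcomes: waist, blood pressure, glucose, HbA1c, triglycerides, HDL, CRP, PANSS, HAM-D, EQ-5D and IPAQ. The trial was sized on weight alone, so the precision available for these is whatever about 70 evaluable participants provide.

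**Working it through.** **1. The plan's own sample size.** Inputs from section 2.9: "We aim to detect a 5% difference in total weight", "assuming a standard deviation of 7.5"%, "Using a power of 80"% and "a bilateral alpha of 5"%.

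- Normal approximation: n per arm = 2 × (1.960 + 0.842)² × (7.5/5)² = 2 × 7.85 × 2.25 = 35.3, so 36 per arm and 72 in total.
- t-based: 36.3, so 37 per arm and 74 in total. The stated 74 reproduces.
- Evaluable after the planned dropout: 88 × 0.80 = 70.4, about 35 per arm.

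The calculation makes no use of baseline adjustment, so it does not depend on this point.

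**2. Variance of the two contrasts.** Let the outcome have variance σ² at each visit and baseline-to-follow-up correlation r, with n per arm.

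- Change-score contrast (the same as group-by-time with free baseline means and complete data): (2σ²/n) × 2(1 − r).
- Baseline-adjusted contrast: (2σ²/n) × (1 − r²).
- Ratio, adjusted to change: (1 − r²)/[2(1 − r)] = (1 + r)/2. Share saved: (1 − r)/2.

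**3. Numbers.** n = 35 per arm, σ = 1. The values of r are assumptions.

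| r | Change contrast | Adjusted | Saving | Equivalent extra participants |
|---|---|---|---|---|
| 0.3 | 0.0800 | 0.0520 | 35% | 54% |
| 0.5 | 0.0571 | 0.0429 | 25% | 33% |
| 0.7 | 0.0343 | 0.0291 | 15% | 18% |
| 0.9 | 0.0114 | 0.0109 | 5% | 5% |

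At r = 0.8 the saving is 10%, and at r = 0.95 it is 2.5%.

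**4. Check through the mixed model itself.** Generalised least squares with three visits (0, 6 and 12 months) and exchangeable correlation gives the change-score variance when baseline means are free. It gives the adjusted variance when they are constrained equal. The savings are 35, 25, 15 and 5% at r = 0.3, 0.5, 0.7 and 0.9, as in the table. A model with a common baseline mean therefore recovers the whole gain without a baseline covariate.

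**5. Illustration in power.** Take r = 0.5, 35 per arm and a two-sided 5% t-test. The SD of the change score is √1.00 = 1.00, and the residual SD after adjustment is √0.75 = 0.866. For a true effect of 0.5 SD, power rises from 54% to 66%. For 0.4 SD it rises from 38% to 48%. Both effect sizes are assumed, since the protocol sets no target for secondary outcomes.

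**6. Chance imbalance.** The standard error of the baseline difference is √(2/35) = 0.24 SD. Given a baseline difference of that size, the change contrast is displaced by (1 − r) × 0.24 in the opposite direction: 0.12 SD at r = 0.5 and 0.02 SD at r = 0.9. Over repeated randomisations this averages to zero.

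**The case against.** The strongest reply is that the article is silent, not wrong. It neither names nor excludes baseline, and a covariate list is commonly left to an analysis plan or full protocol, which are not shown. The sentence on the mixed model is also compatible with a common baseline mean, which would recover the full gain. This stands in part: a reader might infer that the plan discards baseline information, and the text does not support so firm a reading. What remains is that the stated aim, a comparison of changes, leads in its ordinary reading to the less precise contrast, and nothing in section 2.8 steers the analyst away from it.

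Second, the size is not documented. A reader might take 15–35% as a property of all the continuous outcomes. It is only the result for r between 0.7 and 0.3. Strongly correlated measures, plausibly weight in kg, BMI or waist, would gain about 5% or less. This objection stands in full.

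Third, a reader might carry the figures over to the main analysis. They do not apply there: that endpoint is binary and already defined relative to original weight. Nor is the change comparison biased in expectation, because allocation is random. Both points stand.

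**Conclusion.** The point holds as a free gain in precision for the continuous outcomes. The direction is certain for any r below 1 in the linear model. The size rests on an assumed r, equal variances across visits, complete data and the ordinary reading of section 2.8. On those terms the gain is worth having for moderately correlated secondary outcomes in a trial with about 35 evaluable people per arm. The documents do not support calling the present wording an error, a source of expected bias or a threat to the main analysis.

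**What to change.** In section 2.8, state that each continuous outcome at 6 and 12 months is analysed in the linear mixed model with its own baseline value and the baseline-by-visit interaction as covariates. Keeping baseline as a response with a common mean across the arms is an equivalent choice. State also that the adjusted arm difference is reported at each visit with its 95% CI. Table 1 places most baseline measures in the week-1 column alongside the first consultation, so add that they are taken before that consultation begins.

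Adding baseline weight or BMI to the binary 5%-loss analysis is optional, and no gain is claimed for it here.

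The cost is wording only. Every value needed is already scheduled, and neither recruitment nor the sample size changes. The wording should be settled before outcome data are seen by arm.

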## Abstract

**Background**: Individuals with severe mental illness live, on average, up to 30 years less than the general population, with cardiovascular disease being the leading cause of death. Metabolic syndrome (MetS) plays a significant role in this, making it crucial to manage this issue in individuals with psychosis at the onset of the illness. The approach to managing this issue has evolved from a focus on calorie counting to a deeper understanding of hormone function, particularly the role of insulin resistance in MetS. Therefore, incorporating this perspective into mental health nursing consultations with individuals experiencing psychosis is of great interest. **Methods**: In accordance with the SPIRIT guidelines, an open randomized clinical trial is proposed, involving patients from a first-episode psychosis program. **Results**: The primary outcome will be significant weight loss (≥5%). Secondary outcomes will include changes in metabolic parameters, psychopathological status, quality of life, and physical activity. Participants will be assigned to two groups: one group will attend a series of six previously manualized nursing consultations, while the other will continue with their usual treatment. Results will be evaluated at six months and one year. **Conclusions**: This study will determine whether a mental health nursing consultation based on the carbohydrate–insulin model of obesity is effective in reducing weight and the risk of MetS in individuals with early-onset psychosis. This study was retrospectively registered on Clinical Trials—NCT06650943.

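### The 80% power in section 2.9 was computed for a difference in mean percent weight, but the stated main analysis is a yes/no outcome (loss of at least 5%) to which that figure does not apply

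*Protocol article*

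**What the plan says.** Four places in the protocol article describe the primary endpoint or the quantity it was powered for.

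- **Abstract.** A threshold outcome, loss of at least 5%: "The primary outcome will be significant weight loss (≥5" (the quotation stops at the per-cent sign).
- **Section 2.7, Instruments and Variables.** "The primary outcome will be weight loss, with a reduction of 5% considered clinically significant". This can be read as a continuous outcome with a benchmark for interpretation, or as the threshold itself.
- **Section 2.8, Statistical Analysis.** "The main analysis will assess the association between the study group and significant weight loss, defined as losing 5% of the original body weight". This is a binary outcome by study group. The same section names a repeated-measures mixed model, linear or logit according to the variable.
- **Section 2.9, Power and Sample Size.** "We aim to detect a 5% difference in total weight, considering this to be clinically significant", with 80% power, two-sided alpha of 5% and "assuming a standard deviation of 7.5% in an area where evidence is limited". The result is "A sample size of 74 participants will be required to detect this difference", raised to 88 (44 per group) for dropout.

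No responder proportion for either arm appears anywhere, and no power is stated for a binary outcome.

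**The concern.** A difference with a standard deviation sizes a comparison of means. A yes/no outcome is sized from two proportions. Section 2.9 does the first and section 2.8 tests the second. The 5% that marks a worthwhile loss for one person seems to have been reused as the difference between group means, which is a different quantity.

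This matters because reducing percent change to a yes/no outcome discards information. If the intervention shifts mean weight by exactly the planned amount, the main analysis has less chance of detecting it than the comparison that was sized. A null result could then be read as evidence against the intervention by someone who trusts the stated 80%.

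**Working it through.** **1. Reproduce the plan's figure.** Inputs from section 2.9: difference 5, SD 7.5, power 0.80, two-sided alpha 0.05. Standardised difference d = 5/7.5 = 0.667. The normal approximation gives n per arm = 2(1.960 + 0.842)²/0.667² ≈ 35.3, so 36. The t-test version gives 36.3, so 37 per arm and 74 in total, as stated. Power at 37 per arm is 80.8%. The sizing basis is therefore a two-sample comparison of means.

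**2. Translate the same effect into responder proportions.** Assume percent change is normal with SD 7.5 in both arms. Let m be the control mean change (gain positive), which the article does not give, and let the intervention mean be m − 5. A responder has a change of −5% or lower:

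- control: p_C = Φ((−5 − m)/7.5)
- intervention: p_T = Φ((−5 − (m − 5))/7.5) = Φ(−m/7.5)

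Example, m = 0: p_C = Φ(−0.667) = 0.252 and p_T = Φ(0) = 0.500.

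**3. Power at a single visit.** The power columns come from exact binomial enumeration. The last column uses the normal-approximation formula without continuity correction, n = [1.960√(2p̄(1−p̄)) + 0.842√(p_C(1−p_C) + p_T(1−p_T))]²/(p_T − p_C)², where p̄ is the mean of the two proportions.

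| Control mean change | p_C vs p_T | Chi-square, 37/arm | Fisher, 37/arm | Chi-square, 44/arm | n/arm for 80% |
|---|---|---|---|---|---|
| +5% | 0.091 vs 0.252 | 0.465 | 0.351 | 0.545 | 85 |
| +3% | 0.143 vs 0.345 | 0.532 | 0.433 | 0.619 | 71 |
| 0% | 0.252 vs 0.500 | 0.593 | 0.503 | 0.691 | 59 |
| −2% | 0.345 vs 0.605 | 0.613 | 0.519 | 0.680 | 57 |

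At 37 per arm the highest chi-square value among the control means tried is about 61%, near a control loss of 2.5%. With all 88 analysed it reaches about 69%.

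**4. Power if two visits are pooled.** Section 2.8 also names a repeated-measures model, so the responder outcome was simulated at 6 and 12 months and each person's average over the two visits was compared between arms. This is a simple stand-in for a pooled logit group effect. Assumptions: 37 per arm, the same difference and SD at both visits, no missing data, and between-visit correlation ρ from 0.3 to 0.8 (not in the article). Power falls as ρ rises:

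- control +5%: 69% down to about 56%
- control 0%: about 81% down to 71%
- control −2%: 83% down to 72%

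**5. The continuous analysis of the same two visits.** The SD of a two-visit mean is 7.5√((1 + ρ)/2). At ρ = 0.8 this is 7.5 × √0.90 = 7.12, d = 5/7.12 = 0.70, power about 85%. At ρ = 0.3 it is 7.5 × √0.65 = 6.05, d = 5/6.05 = 0.83, power about 94%. In every scenario tried, the responder version has less power than this.

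**The case against.** Three points can fairly be made for the plan.

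First, section 2.7 is where outcomes are defined, and it says weight loss, with 5% as a benchmark. Read as continuous, it agrees with section 2.9, and the Abstract and section 2.8 are then out of step. This stands as a reason not to presume which endpoint was intended. It does not remove the problem, because section 2.8 says outright what the main analysis is and would then need correcting.

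Second, the single-visit figures are not the power of the repeated-measures model in section 2.8. This also stands. A reader might infer that the trial's true power is 47–61%, or that the main test is a coin flip. The article does not support that: it ties the main analysis to no single visit, gives no control mean and gives no visit correlation. In the most favourable pooled scenarios (low correlation, control weight stable or falling) the responder analysis reaches just over 80%. But section 2.9 does not rely on pooling, so this would not be the 80% it states.

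Third, a separate analysis plan might settle the endpoint. It could, but the protocol itself states both the main analysis and the power, and the two do not match. This is a contradiction in the text, not a detail left for later.

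The choice of a responder endpoint is not itself the error. Loss of at least 5% is a legitimate outcome if the trial is powered for it.

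**Conclusion.** The mismatch is established from the text and from exact reproduction of N = 74: the stated 80% belongs to a comparison of means and does not carry over to the responder analysis that decides the trial. How far power falls is conditional. Assuming normality and the plan's own difference and SD, it is about 47–61% for a single-visit chi-square at 37 per arm, over control mean changes from a 5% gain to a 2% loss, and at most about 69% with all 88 analysed. It is roughly 56–83% for a pooled two-visit analysis under assumed correlations of 0.3–0.8 and a constant effect. None of these is the trial's actual power. What holds across the scenarios is that the responder analysis has less power than the continuous analysis of the same data, and that the plan gives no basis for claiming 80% for it.

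**What to change.** Before outcome data are examined, and with a dated justification in the protocol and the registry, name one primary endpoint consistently in the Abstract and sections 2.7, 2.8 and 2.9.

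- **Preferred.** Primary: the between-arm difference in percent weight change from baseline at a stated time point, from a linear mixed model adjusted for baseline weight. This is the kind of endpoint N = 74 was computed for. Loss of at least 5% becomes a secondary responder outcome.
- **If the responder outcome stays primary.** State the assumed proportions in each arm and the time point in section 2.9, and replace 80% with the power for that analysis (about 47–61% for a single-visit comparison). Reaching 80% at one visit would need about 57–85 analysed per arm under the scenarios above.

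Cost: the preferred option needs no new patients or measurements, since Table 1 already lists weight at every visit. It makes the responder rate supportive, and it is a change of primary outcome relative to the Abstract and section 2.8. Because the trial is open-label and was registered retrospectively, that change must be documented and dated, not made as a silent rewording.
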